## Introduction

1

As lead is one of the few substances that does not have a safe level of exposure, it is important to minimize all exposure [1], [2]. Hunters can use lead or lead-free bullets [3], and a vast majority choose to use lead bullets [4], [5], primarily because of tradition and the belief that lead bullets are safe. Non-lead projectiles are considered premium ammunition [6], but they are not significantly more expensive in some world areas [7]. There is a correlation between hunters using lead projectiles and elevated lead blood levels [8], [9], [10], however a causal link is unestablished [11]. As lead-shot meat is sold globally, this potential lead contamination is a global health concern [12].

This is a clinical research protocol to determine the feasibility of assessing lead levels in hunters who use lead projectiles. This observational study will determine if it is possible to perform a subsequent interventional blinded controlled study of lead levels in hunters using lead or lead-free projectiles following consumption of self-harvested wild game. The hypothesis for the subsequent study is that minute lead particles from shrapnel dispersed through the animal during harvest are ingested and this exposure results in increased lead blood levels [3]. This current observational study will establish the sample size and washout period for the subsequent interventional study. This observational study will be conducted in compliance with the protocol, Good Clinical Practice Standards, associated regulations and institutional research requirements.

There are three biological compartments where unexcreted lead is stored: blood, soft tissue, and mineralising tissues. After absorption, lead is stored in the blood compartment with a half-life of 28 [13] – 36 [14] days. Lead rapidly disperses into soft tissues post-exposure and in soft-tissues it has a half-life of approximately 40 days [15]. The primary long term repository of lead in the body is mineralizing tissue in bones and teeth [16]. Importantly, these mineralizing tissue stores can be mobilized and increase lead levels in the blood. The long half-life of lead and the dynamic nature of storage with the various compartments present challenges in identifying causal relationships between lead exposure and blood lead levels.

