This current study establishes the parameters necessary to assess whether hunters eating meat shot with lead projectiles have elevated blood lead levels. For this feasibility study, hunters will be asked to abstain from consuming meat harvested with lead projectiles for 7 days. After 7 days, hunters will provide a baseline blood sample. Hunters will then consume meat that was harvested with lead projectiles and provide an additional blood sample 2–4 days (the blood-lead level peak post exposure [17]) after consumption. Hunters will also provide subsequent blood samples at periods of 9, 18, and 27 days. During the 27 day period, hunters will not consume meat harvested with lead projectiles. (Fig. 1). We have chosen to use deer as the species for this study to reduce variation; New Zealand is the ideal place to conduct this study because of year-round hunting of deer [18]. This study design will allow for the development of a conditional linear effects model, which will account for the inherent correlation of longitudinal data that involves repeated measures on the same subject over a period of time. A conditional model will also be more robust to any missing data that may arise through the course of the study, which may also facilitate a reduction in the required number of subjects necessary for this feasibility study.

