### Study objectives

2.1

The primary objective of this observational study is to determine the washout period and sample size for a subsequent study measuring lead levels in hunters in New Zealand after eating wild game shot with lead projectiles. This primary objective will be accomplished through measuring lead levels in hunters who have recently eaten meat harvested from deer killed with lead projectiles and subsequently measuring blood lead levels of those same hunters after abstaining from eating meat harvested from deer killed with lead projectiles (Fig. 1).

The secondary objective is to determine the feasibility of a blinded controlled interventional trial comparing blood lead levels in hunters using lead and lead-free projectiles for harvesting wild game for consumption. Specifically, this aspect of feasibility will be determined by participant compliance during this feasibility study.

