### Primary outcome and sample size determination for the feasibility study

2.6

A two-tailed dependent *t*-test was utilized to perform a power analysis and determine sample size necessary for the study. A dependent *t*-test was used for the power analysis in order to ensure sample size would not be underestimated. To address correlation and the nature of longitudinal data, a conditional linear effects model will then be utilized to determine differences in the pattern of mean blood lead level over time. A sample size calculation was performed (SigmaPlot 12.5; Systat) and the following values were assigned based on previous literature and clinical logic: Expected Difference in Means: 0.074; Expected Standard Deviation: 0.19; Number of groups: 2; Desired Power: 0.8; Alpha: 0.05. The expected mean difference is derived from preclinical data [17] and 7 day washout. This calculation resulted in a sample size calculation of 54 data points in each abstention cohort.

We expect 25% attrition from the study and therefore we will be required to recruit a total of 68 participants.

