### Statistical methods and analysis of feasibility study

2.7

All data will be summarized using descriptive statistics (i.e. mean ± SEM). Data will be tested for normal distribution using a QQ plot and the Shapiro-Wilk test. Visualization and assessment of normality will be achieved through creation of histograms and boxplots. The primary dependent variable is mean blood lead level. In order to determine whether there is a difference in the pattern of mean blood lead level over time while accounting for lead exposure, mean blood lead level at baseline, 2–4 days, 9 days, 18 days and 27 days will be analysed using a conditional model that will account for the correlative nature of longitudinal data involving repeated measures taken from the same subject. This model is advantageous for a variety of reasons, including that this approach can handle unbalanced data (missing data at various time points), as well as continuous and discrete predictors. This model will also be able to model covariance structure which is important when handling correlated data. A random intercept will be utilized to account for natural variation in baseline blood lead measurements among hunters. Predictors will include the grouping variable of lead vs. lead-free projectile, time and the interaction of group and time. The interaction term will allow the investigators to identify whether blood lead level changes over time, thereby determining the most appropriate wash-out period. Other factors, such as any exposure to lead ammunition and isotope analysis may be included as factors in the analysis.

Categorical variables will be analyzed using chi-square tests. Variables including (agree to participate in study/decline to participate because of request to abstain/not because of request to abstain) will be used to determine the feasible length of abstaining from eating wild-shot meat. This value is important in determining the washout period for the interventional study. Adjustments using Fisher exact tests will be utilized to account for any cell counts that are 5 or less.

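### Section 2.7 ties the washout to a test of whether blood lead changes over time, which cannot show that a period is long enough; no limit on residual lead is set

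*Protocol article*

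**What the plan says.** Section 2.1 states: "The primary objective of this observational study is to determine the washout period and sample size for a subsequent study". Section 2.6 says that "a conditional linear effects model will then be utilized to determine differences in the pattern of mean blood lead level over time", and section 2.7 applies the model to baseline, 2–4, 9, 18 and 27 days. On the washout, section 2.7 says: "The interaction term will allow the investigators to identify whether blood lead level changes over time, thereby determining the most appropriate wash-out period".

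Two other inputs to the choice appear. The legends of Figs. 1 and 5, section 3 and the Discussion say that the blood levels will give a sample size for each candidate washout. Section 2.7 also uses data on agreeing or declining to abstain. Section 3 names five half-lives as the usual standard and sets it aside as not feasible. Nowhere does the article give a maximum residual, a margin, or a rule that turns the model result into 9, 18 or 27 days.

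Separately, the term named is a group-by-time interaction, and this study has no lead-free group. If the group term is dropped, a time effect is left, and the point below applies to that.

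**The concern.** A washout period is adequate when little enough of the earlier exposure remains for the next comparison. That is a statement about the size of a residual. A test of change answers a different question, and neither result settles the matter:

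- **Non-significant against baseline.** This may mean that lead has returned to baseline, or that the study could not see the excess.
- **Significant fall from the 2–4 day draw.** This shows that some lead has gone, not that little is left.
- **Significant effect over all five draws.** This mostly reflects the step from baseline to the post-meal level.

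The chosen period passes directly to a crossover trial with repeated meal cycles, where lead left from one cycle enters the next baseline.

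**Working it through.** **Inputs.** Half-life (Introduction): "lead is stored in the blood compartment with a half-life of 28 [13] – 36 [14] days". Post-meal draw: "provide an additional blood sample 2–4 days (the blood-lead level peak post exposure [17]) after consumption". Later draws: "Hunters will also provide subsequent blood samples at periods of 9, 18, and 27 days". Planning values (section 2.6): "Expected Difference in Means: 0.074; Expected Standard Deviation: 0.19; Number of groups: 2; Desired Power: 0.8; Alpha: 0.05". Test: "A two-tailed dependent *t*-test was utilized to perform a power analysis".

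**1. The plan's own figure.** A two-sided paired t-test has non-centrality (0.074/0.19)·√n. At n = 54 the power is 0.802, which reproduces the stated 54. So 0.19 acts as the SD of within-person change, with standard error 0.19/√54 = 0.0259.

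**2. Share of the meal's lead remaining.** First-order decay is assumed. Counted from the post-meal draw, the share is r = 2^(−w/HL). Counted from the meal with a day-3 peak, it is r = 2^(−(w−3)/HL). The article can be read either way.

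| Day w | From draw, HL 28 / 36 | From meal, HL 28 / 36 | Range |
|---|---|---|---|
| 9 | 80% / 84% | 86% / 89% | 80–89% |
| 18 | 64% / 71% | 69% / 75% | 64–75% |
| 27 | 51% / 59% | 55% / 63% | 51–63% |

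These shares do not depend on what 0.074 means.

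**3. Non-significance against baseline (illustration only).** Suppose that 0.074 is the rise from one meal and that a non-significant draw were taken as washed out. The chance of non-significance is 1 − power at non-centrality r·0.074/0.0259. For r = 0.513 this is 1.47, giving 70%. Over both ways of counting days and both half-lives:

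- day 9: 29–39%
- day 18: 44–56%
- day 27: 58–70%

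Suppose instead that 0.074 is a decline over 7 days. The peak is then 0.074/(1 − 2^(−7/HL)) = 0.47 (28 days) or 0.59 (36 days). The day-27 residual, counted from the draw, is 0.24 or 0.35, and non-significance against baseline is close to 0%.

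**4. A significant fall from the post-meal draw.** With days counted from the draw, under the 7-day-decline reading the fall by day 9 is 0.093 and is significant in about 94% of studies, while 80–84% of the meal's lead remains. Under the one-meal reading the fall by day 27 is significant in 21–28%.

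**5. What the five-draw test detects.** Take the one-meal reading, half-life 28 days, days counted from the meal and visit-level variance 0.19²/2 = 0.01805. The expected excesses are 0, 0.0740, 0.0638, 0.0510 and 0.0409. Their sum of squares about the mean is 0.00327, so λ = 54 × 0.00327/0.01805 = 9.8, and the power of F(4, 212) is about 69%. For the four post-meal draws alone the sum of squares is 0.00063, so λ = 1.9, and the power of F(3, 159) is about 18%. About four fifths of the signal (1 − 1.9/9.8) is therefore the contrast of baseline with the later draws.

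**6. What n = 54 can support.** The 95% half-width for a mean change is 2.006 × 0.0259 = 0.052, or 70% of 0.074. The Fieller interval for the residual fraction ρ solves (m_d − ρ·m_p)² = t²(v_d − 2ρc + ρ²v_p). Here m_d and m_p are the mean changes from baseline at day 27 and at the 2–4 day draw, v_d = v_p = 0.19²/54 and c = v_d/2. With data exactly at the planning values and days counted from the meal, it runs from −0.25 to 1.46 (28 days) or −0.11 to 1.62 (36 days).

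**The case against.** A reader might infer that the plan treats non-significance as washout, so that imprecision shortens the washout and a period with over half the lead left will often be accepted. The document does not support this. Section 2.7 names no test of each draw against baseline and never says that a non-significant result means washed out. If a significant fall were required instead, imprecision would count against washout. The rates in step 3 of the working belong to a supposed rule. They also rest on reading 0.074 as the rise from one meal. Section 2.2 supports this by basing the calculation on the 85 g serving, but section 2.6, which cites preclinical data and a 7-day washout, leaves it open.

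Nor is the test the only route to the washout. The plan also weighs sample size per period and willingness to abstain, and by setting five half-lives aside it openly accepts incomplete washout. That is fair, but such a trade-off needs an estimate of the residual, and neither route limits it.

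A single linear slope for time could not represent a rise and fall. However, the article does not say that time is coded that way: section 2.7 lists five visits and allows discrete predictors, so this is not counted as a flaw. Margins are often left to an analysis plan. Here, though, the protocol itself states a criterion, and that criterion does not answer the question.

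Finally, the successor trial takes a new baseline before the meal, so carry-over can be partly allowed for. This lowers the stakes.

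**Conclusion.** The point holds: the stated inferential criterion cannot identify an adequate washout whichever way its result is read, and no other part of the article limits residual lead. This rests on the text and needs no assumption about 0.074. The size of the problem is the residual itself: about 80–89%, 64–75% and 51–63% of the meal's lead at days 9, 18 and 27, assuming first-order decay at the plan's half-lives.

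How often a poor period would be chosen cannot be settled. It is 29–39%, 44–56% and 58–70% under one supposed rule and one reading of 0.074, and near zero at day 27 under the other reading. This should be fixed because it concerns the primary objective, but it does not undermine the data to be collected.

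**What to change.** Replace the quoted sentence in section 2.7 with the following:

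- Model time as the five visits.
- For 9, 18 and 27 days, estimate the residual above baseline and the residual fraction (draw minus baseline, divided by the 2–4 day draw minus baseline), each with a 95% interval (Fieller, or bootstrap over hunters).
- Carry these estimates into the sample size for each candidate washout.
- State that neither a non-significant nor a significant time effect is by itself evidence of washout.
- Call a period adequate only if the upper limit lies below a margin fixed before the data are seen. Otherwise report the washout as not determined and give the residual expected from the 28–36 day half-life.

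The cost is wording and a few lines of analysis, with no new data. The downside is real. Simulation at n = 54 under the one-meal reading puts the upper Fieller limit below 0.50 in about 30% of studies even when the true residual is zero, and in about 1% at a day-27 residual of 55–63%. Showing a true zero residual to be below 50%, 25% or 20% of 0.074 (80% power, one-sided 0.05) needs n = ((1.645 + 0.842) × 0.19/(f × 0.074))², where f is the limit as a share of 0.074: about 164, 653 or 1,019. The protocol should say in advance that an undetermined washout is the likely result.

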### General study design

2.2

There are two periods of analysis for this study.1.Hunters that within 2–4 days prior to blood being drawn have eaten self-harvested wild deer shot with lead projectiles; and2.Hunters that have abstained from eating self-harvested wild deer shot with lead projectiles for specific periods of time.

Hunters in period 1 and period 2 are the same individuals; they will be consented for the study once they have harvested an animal and provide pictures of shot placement. In order to avoid bias, the investigator performing the data analyses and the laboratory staff will be blinded to the samples. The participants will know when they are submitting blood samples during the period while eating meat harvested with lead bullets and when they are submitting blood samples while abstaining from lead-harvested meat so they will not be blinded. Animals will be shot in the thorax (Fig. 3) and the hunter will provide photographs of the shot location. Hunters should process the animal according to their standard practice, including making of minced meat.

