**Fig. 4 fig4:**
[figure not shown]
**Resource created for hunters interested in participating in the study.** For outreach and to facilitate participant recruitment, bi-fold business-card sized information sheets that can be kept with the potential participant's firearms license are being created. The front and the back of the resource is shown.

It will be explained to hunters that after they shoot an animal that they must take a photograph of the animal to document shot placement. The photograph will be at least 72dpi resolution and clearly identify the location the animal was shot. The hunters must provide the weight of their bullet (brand if possible) and number of shots used to harvest the animal. This step is important to verify shot placement, and also to confirm the ability of the prospective participant to follow the directions for the study. The pictures indicating shot placement will be emailed to [contact] with the hunter contact information and a time available for a phone call. All hunters that send pictures will receive a phone call from the study coordinator.2.Consent to enrol in study

Hunters that successfully email photographs of the harvested animals with the required information will be interviewed by the study coordinator for enrollment in the study. Enrollment in the study will occur in two steps. First, a telephone call will explain to the participant the consent form (see supplemental data) and answer questions the participant has regarding the study. The participant will be asked approximately how many times per week they eat lead-shot animals and if they are willing to abstain from eating lead-shot meat for 9, 18, or 27 days. Second, if the participant is still interested in participating, a consent form will be mailed to the participant and a time will be scheduled for a subsequent telephone call to allow formal consenting of the participant. Preliminary discussions with hunters have determined that a majority would be willing to abstain from eating wild-shot meat for one month for the study. However, if hunters decline to participate based on the length of abstaining from eating wild meat, they will be offered to still participate and abstain from eating lead-shot meat for 9 days (or the maximum they are willing to abstain). The consent form package will include a postage-paid envelope.

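### The agree/decline variable and the chi-square or Fisher tests named for it cannot show which abstention length is feasible; report the proportion accepting each length instead

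*Protocol article*

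**What the plan says.** Section 2.7 (feasibility study analysis) states: "Categorical variables will be analyzed using chi-square tests". The same paragraph names the response of interest as "agree to participate in study/decline to participate because of request to abstain/not because of request to abstain" and says that it "will be used to determine the feasible length of abstaining from eating wild-shot meat". It adds: "This value is important in determining the washout period for the interventional study". The paragraph closes with the small-sample variant: "Adjustments using Fisher exact tests will be utilized to account for any cell counts that are 5 or less". It gives no other method for this response and no proportion that would count as acceptable.

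Section 2.5, step 2, describes how the response arises. In the enrolment telephone call each hunter is asked about willingness to abstain for 9, 18 or 27 days. There is then a fallback: "if hunters decline to participate based on the length of abstaining from eating wild meat, they will be offered to still participate", for 9 days or for the longest period they will accept.

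Section 2.1 makes the washout period and sample size of the later trial the primary objective.

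**The concern.** The question is how long hunters will abstain, and its answer is a number of days. The variable assigned to it records whether a hunter joined and, if not, whether the abstention request was the reason. Length does not appear in it. A chi-square or Fisher test on that variable gives a p-value for equal category frequencies or for association with some other variable. Neither is a length.

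The fallback makes this worse. A hunter who turns down 27 days and then enrols for 9 days may be counted as agreeing, so even the plain percentage agreeing does not say what was agreed to.

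At stake is one of the two inputs to the washout of the interventional trial: what hunters will tolerate, as distinct from what the blood lead curve requires. If only the three categories are tabulated and tested, that input will not be available when the washout is chosen.

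**Working it through.** The protocol states no sample size, threshold or power for this analysis, so there is no planned figure to reproduce. The 54 data points and 68 recruits in Section 2.6 belong to the paired blood lead comparison. The number of hunters to be telephoned is not given. The counts below are illustrative. They happen to total 68, but nothing rests on that: 68 is a recruitment target, and hunters who decline are not recruits.

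**Step 1: what a test on the response alone returns.** For three categories with observed counts O and N hunters in all, the goodness-of-fit statistic against equal frequencies is Σ(O − N/3)² / (N/3), on 2 degrees of freedom.

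- Counts 50/10/8 (agree / decline for abstention / decline for another reason), N/3 = 22.667: (27.333² + 12.667² + 14.667²) / 22.667 = 1122.67 / 22.667 = 49.5; p = exp(−49.53/2) = 1.8 × 10⁻¹¹.
- Counts 8/50/10: the same three numbers in another order, so again 49.5 and p = 1.8 × 10⁻¹¹.

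The first set is wide acceptance and the second is wide refusal because of abstention. The statistic ignores which category holds which count, so it cannot tell them apart.

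**Step 2: what the three categories can say about length.** Let a be the number agreeing, d the number declining because of abstention, and s the number who refused 27 days but took the fallback. The protocol does not say how those s hunters are coded.

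- If they count as agreeing, the proportion accepting 27 days is (a − s)/N. Since s is not in the variable, a = 50 and N = 68 allow anything from 0 to 50/68 = 74%.
- If they count as declining because of abstention, a/N does describe 27 days. The proportion accepting at least 9 days is then only known to lie between a/N = 50/68 = 74% and (a + d)/N = 60/68 = 88%.

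Under either coding the acceptance curve over 9, 18 and 27 days cannot be recovered, and no test changes that.

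**Step 3: if acceptance were compared across lengths.** The protocol does not propose this, but an analyst might turn to it. The same person answers for all three lengths, and willingness for 27 days is taken to imply willingness for 18 and 9, so the answers are nested within hunter. Suppose 60, 54 and 50 of 68 hunters accept 9, 18 and 27 days:

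- Chi-square treating the three rows as separate hunters: 4.73 on 2 df, p = 0.094.
- Cochran's Q, which respects the nesting. There are 50 hunters with three acceptances, 4 with two, 6 with one and 8 with none. Q = 2 × [3 × (60² + 54² + 50²) − 164²] / [3 × 164 − (50×9 + 4×4 + 6×1)] = 2 × 152 / 20 = 15.2, p = 0.0005.

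The independence assumption matters. Even the valid test shows only that acceptance falls with length, not which length is acceptable.

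**The case against.** The test and the length are linked only by adjacency. The text says that the variables will be used to find the feasible length; it does not say that a p-value will supply it. Section 2.7 also opens by promising descriptive summaries of all data, which leaves room for proportions. The list of variables is introduced as open, and the mention of Fisher tests suggests cross-tabulations, for example against how often a hunter eats lead-shot meat. Choosing such tables is ordinary content for an analysis plan that is not shown. The washout is also to be informed by the blood lead model, so willingness is only one contributor.

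All of this stands as a limit on the point. It would be wrong to say that a chi-square test has no possible use here. The core remains, because the document itself names the variable and its purpose. Neither a descriptive summary nor a cross-tabulation of three categories without days gives a length.

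A reader might go further in three ways that the documents do not support.

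- **No comparison group.** A second group would not turn a chi-square test into a length, so its absence is not the fault.
- **An invalid chi-square across 9, 18 and 27 days.** No such comparison is planned; Step 3 is a caution only.
- **Inflated compliance.** Section 2.1 says that "this aspect of feasibility will be determined by participant compliance during this feasibility study", and one could suppose that a hunter who chose 9 days and kept to 9 days would score as fully compliant. Nothing says compliance is judged against a self-chosen length. Section 2.3 lists compliance with the study protocol, and Section 2.5 instructs draws at 9, 18 and 27 days.

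**Conclusion.** The point holds as a minor one. For the feasible abstention length, the protocol names a variable that carries no days, and its only named method for categorical data is a test that cannot supply them. The fallback offer leaves it unclear what an agreement means.

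The effect cannot be expressed as a bias or an error in a proportion, because the number telephoned and the likely split of answers are not given. What can be said is that the three categories leave the acceptance curve undetermined under either coding of the fallback, and that the goodness-of-fit result is identical for wide acceptance and wide refusal. This rests on reading the chi-square and Fisher sentences as covering the response named between them, which is the natural reading since no other method is offered.

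The study's ability to choose a washout is not lost. The blood lead model still contributes, and the telephone interview already raises the lengths in question.

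**What to change.** For this question, replace the chi-square and Fisher tests in Section 2.7 with the following:

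- Record, for every hunter telephoned, the longest abstention they would accept (none, 9, 18 or 27 days, or another stated maximum), whether or not they enrol, and keep the reason for declining.
- Report the cumulative proportions accepting at least 9, at least 18 and 27 days, each with an exact 95% confidence interval, using all hunters telephoned as the denominator.
- State how a hunter who refuses the longer period and enters through the fallback is classified.
- If acceptance is compared across lengths, use a method that treats the answers as nested within hunter.

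Chi-square or Fisher tests can stay for other categorical comparisons. The cost is small: a change of analysis wording, one recorded item from a conversation already planned, a log of all hunters telephoned and slightly longer reporting. Visits, blood draws and the blood lead sample size do not change.
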